## Abstract

**Background:**

*Remaking Recess (RR)* is a school-based evidence-based peer social engagement intervention for autistic students. *RR* involves direct training and coaching with educators; however, educators face several barriers to implementation at both the individual- and organizational-levels. This protocol paper describes a multi-site study that will test whether an educator-level implementation strategy, *coaching*, with or without a school-level implementation strategy, *school-based teams*, will maximize educators’ use (fidelity and sustainment) of RR for autistic students and their peers who are socially-isolated, rejected, or peripheral and may need additional support during recess.

**Methods:**

This study will employ a hybrid type-3 effectiveness-implementation trial. Fifty-five elementary schools will be recruited as well as 121 educators (e.g., classroom assistants, aides), 55 general and special educator teachers, and 83–138 other school personnel (e.g., administrators). Additionally, at least 118 autistic students and allistic or non-autistic classmates will be recruited as *RR* recipients. Participants will complete baseline assessments at the beginning of the year, and all schools will be provided *RR* training. Schools will be randomized to coaching with or without school-based teams. This study will measure *RR* fidelity (primary outcome), *RR* sustainment, as well as peer engagement, social network inclusion, and social skills (secondary outcomes). It is expected that coaching with school-based teams will improve both *RR* fidelity and social network inclusion, while coaching with and without school-based teams will result in improved peer engagement and social skills.

**Discussion:**

Previous research has documented barriers to *RR* implementation at both the individual- (provider) and organization-level (school). Using multi-level implementation strategies such as coaching with school-based teams may address these barriers and support RR implementation in schools. Findings from this study may guide future efforts to scale up tailored implementation strategies for use in public school districts, with the ultimate goal of increasing intervention access and improving student outcomes.

**Trial registration:**

**Name of the Registry:** clinicaltrials.gov.

**Trial Registration:** Clinical Trials ID: NCT06559267.

**Date of Registration:** August 15, 2024. Prospectively registered.

Contributions to the literature
Remaking Recess (RR) is an intervention that improves peer engagement and classroom inclusion in autistic students. Educators, who play an important role in supporting autistic youth and their peers who are socially-isolated, rejected, or peripheral during the school day and at recess, can deliver RR.Schools face many challenges, at both the individual- (i.e., educator) and organizational-levels (i.e., school), when implementing new interventions.This study will evaluate the impact of two implementation strategies on the fidelity and sustainment of RR: (a) individual direct coaching for educators (coaching), and (b) supporting a team of school personnel (school-based teams) in addition to coaching.

## Background

Autism affects 1 in 36 youth in the USA and is the fastest growing segment of the school population [1, 2]. Schools are under increasing pressure to provide evidence-based practices (EBPs; i.e., services that have been proven efficacious in research trials), to meet the diverse needs of autistic students [3, 4]. Social emotional learning (SEL) skills are crucial for students to feel safe and included in school [5]. While autistic students often are the focus of social skills EBPs, they are not the only students having difficulties with peer engagement, particularly post-pandemic. In inclusive settings, nearly one-third of the classroom are isolated or peripheral on social network measures [6–8]. Moreover, strategies used to help autistic students (e.g., use of explicit language, visual supports) have long been advocated to help all students. Thus, teaching educators to apply strategies across all students will improve the recess environment for all, which the American Academy of Pediatrics describes as a crucial component of children’s development [9]. Few social engagement EBPs have been tested in the school environment that also include allistic or non-autistic classmates [10–13].

Educators can be effective change agents in schools and are able to support autistic students and their peers during recess [14–16]. In a report including 313 educators that work with students with disabilities, nearly 90% reported their role was to facilitate social relationships [17]. Although most educators are not provided access to autism-specific professional development, those who receive personalized instruction can improve student academic and social outcomes [18–20].

Studies highlight individual- and organizational-level barriers impacting successful EBP implementation and sustainment [6, 16, 21–26]. For example, lack of training and resources (e.g., staff, materials) may hinder successful EBP implementation and sustainment in schools [27–29]. The transition back to in-person learning has been an additional barrier to successful EBP implementation (e.g., social distancing requirements) as educators readjusted to new policies in the wake of the COVID-19 pandemic [30]. Social engagement interventions also have distinctive barriers; they often are delivered during recess, and schools may have unique policies around recess (e.g., detention during recess), staff allocation (e.g., prioritization of competing staff demands), and the availability and accessibility of resources (e.g., playground materials) that interfere with implementation [31, 32]. Solutions generated in partnership with school-based teams with expertise in the local context will be important to problem solve school-specific barriers to implementation. Overall, there is a need to better understand implementation facilitators, such as implementation strategies linked to underlying educator- and school-level mechanisms of change, to increase sustainability and student outcomes [15, 16, 33, 34].

### Remaking Recess

Remaking Recess (*RR,*
http://www.remakingrecess.org) [35] is a school-based social engagement intervention that improves peer-related social skills for autistic students. *RR* combines peer-mediated and adult-facilitated approaches in schools. *RR* occurs over 10 sessions (Table 1) and is individualized to each student’s needs. *RR* was developed in partnership with two autistic researchers and a community advisory board that comprise autistic self-advocates, parents/caregivers, and educators.

**Table 1 Tab1:** Remaking Recess Modules

Module	Session	Module Topic
1	1	Assessing school’s recess environment, including how school rules and policies affect recess
2	1	Identifying optimal school staff to deliver Remaking Recess
3	2	Gathering information about students for participation in Remaking Recess
4	2	Understanding the reasons why recess may be hard for autistic students
5	3	Increasing your social power at recess with autistic students and their peers
6	3	Identifying student(s) at recess who may need support to play with peers
7	4	Supporting transitions of student(s) to and from recess
8	5	Identifying peer models
9	6	Providing engaging and common games and activities during recess
10	7	Providing in vivo social skills instruction and support to autistic students at recess
11	8	Facilitating peer conversations with student(s)
12	9	Building flexibility in student(s) during recess
13	10	Managing behavior during recess

*RR *has been tested in five randomized controlled trials in public schools and has demonstrated significant improvements in autistic students’ peer engagement with effect sizes between 1.2 and 2.4 [15, 16, 34, 36]. Three studies indicated that it was feasible to train educators in *RR*, that educators increased their knowledge and skills to improve peer engagement of autistic students, and that students decreased isolation during recess [34, 35]. Studies of allistic students show that they have improved playground engagement (increased from 65 to 75%) and are more likely to be connected to autistic students on their classroom social network after *RR *participation while maintaining high scores on all other social outcomes [36, 37].

Educators experience many barriers to implementation including poor implementation leadership (specific leader behaviors that support EBP implementation) and implementation climate (perceptions on whether use of an EBP is expected, supported, and rewarded) [38, 39] resulting in intervention use with varying fidelity and limited sustainment [16, 31, 32]. To address this, a small-scale pilot randomized controlled trial of two implementation strategies, educator-level coaching and school-based teams, was conducted [33, 40, 41]. In coaching, a trained member of the research team provided direct coaching to educators in *RR*; and in school-based teams, a trained member of the research team provided implementation support to a small team of school personnel (administrators, teachers) to support *RR *use [16]. Autistic students in both conditions (coaching with or without school-based teams) showed significant reductions in solitary engagement and increased peer engagement (ES = 0.8). However, autistic students in schools that received school-based teams had better class-wide, social outcomes (i.e., social network inclusion; ES = 0.41). Additionally, higher observer-rated fidelity was associated with more peer engagement, where autistic students that received *RR *with high fidelity engaged with peers more consistently [42]. These results suggest that school-based teams may have a positive effect on student-level outcomes above and beyond coaching alone, and that further research is needed to understand the effects of coaching and school-based teams on successful implementation in a larger trial.

### Theoretical framework and approach

The Consolidated Framework for Implementation Research (CFIR) was used to guide study aims and assess the implementation context (elementary school settings) and evaluate implementation progress (monitor educators’ *RR *use) [43]. Specific CFIR components included: 1) the intervention (*RR*); 2) inner setting (schools); 3) the individuals involved (educators and school-based teams); 4) the implementation process; and 5) outer setting (e.g., school district variables associated with cost). The implementation strategies comprise coaching, once weekly coaching in *RR* and school-based teams, monthly facilitation of school-based teams that identifies, monitors, selects, and matches implementation strategies to address common barriers to *RR *implementation. We theorize that: 1) coaching targets the educator-level mechanism [44], skill acquisition (learning to use *RR*); and 2) school-based teams target school-level mechanisms, implementation leadership and climate, which will directly impact educators’ use of *RR* with fidelity that ultimately will lead to improved student outcomes (Fig. 1). Implementation leadership and climate are proposed school-level mediators in the theory of change. We will measure three implementation outcomes: 1) *fidelity*, the degree to which *RR* is used in the way it was designed during the active implementation phase (primary outcome); 2) *sustainment*, the extent to which *RR* use is maintained the following school year; and 3) *cost,* the extent of resources needed for an implementation effort [45] and three student outcomes: 1) *peer engagement*; 2) *social network inclusion;* and 3) *social skills*. We focus on social outcomes that are most relevant to school inclusion [4, 6, 6, 8].

**Fig. 1 Fig1:**
[figure not shown]
Theorized mechanisms of change

#### Study purpose and aims

The purpose of this study is to test whether an educator-level implementation strategy, *coaching*, with or without a school-level implementation strategy, *school-based teams*, will maximize educators’ use (fidelity) of *RR* and student outcomes.

**Primary Aim 1:** Test the effect of coaching with school-based teams (vs. coaching only) on educators’ implementation and student social outcomes. We hypothesize that (a) coaching with school-based teams will result in greater *RR* fidelity (primary outcome) at the end of Semester 2 and sustainment the following school year, and (b) both arms will result in improved peer engagement and social skills from baseline to end of Semester 2, but coaching with school-based teams will improve student social network inclusion at the end of Semester 2 more than coaching.

**Secondary Aim 2: (Mediation)** Test the extent to which implementation leadership and climate will mediate the effect of coaching with school-based teams vs. coaching only on implementation and student outcomes. We anticipate that both implementation leadership and climate will mediate the relationship between coaching with school-based teams and coaching only and *RR* fidelity and student social outcomes at the end of Semester 2.

**Secondary Aim 3: (Moderation)** Explore if subgroups of students will benefit more from *RR *implementation by examining whether child-level characteristics (e.g., age, gender, autism classification) moderate the effect of coaching with school-based teams vs. coaching only on implementation and student outcomes. Based on our previous research [46], we anticipate that younger vs. older, female vs. male, or allistic vs. autistic students in schools that receive coaching with school-based teams will have better student social outcomes compared to coaching only.

**Secondary Aim 4**: Estimate the incremental costs of coaching with school-based teams versus coaching only to determine the most cost-effective approach.

## Method

A hybrid type 3 effectiveness-implementation trial will be conducted (Fig. 2). After baseline assessments at the beginning of the school year, all schools will be provided *RR* training (Table 2). Schools will be randomized to coaching with school-based teams or coaching only.

**Fig. 2 Fig2:**
[figure not shown]
Study design

**Table 2 Tab2:** Variables, measures, and timepoint of collection

Variable	Measure	Data Source	Timing	Var Type	Potential Operationalization
**Demographics and Context**					
School characteristics	Adm	Rec	T1	Cont	School enrollment; % students receiving free or reduced-price meals; % students with disabilities
Educator characteristics	Demo Survey	Para Teach TEAM	T1	Cont Cat	Age; Years of experience; Level of training (1 = HS, 2 = AA, 3 = BA, 4 = MA, 5 = PhD); Gender identity (1 = Male, 2 = Female, 3 = Other); Race (1 = Black, 2 = White, 3 = Asian, 4 = American Indian/Alaska Native, 5 = Hawaiian/Pacific Islander, 6 = Other); Ethnicity (Hispanic or Latino = 1, Not Hispanic or Latino = 0)
Student characteristics	Demo Survey	Parent	T1	Cont Cat	% time in inclusion; Age; Gender identity; Race; Ethnicity (same as above)
Autism classification	SCQ	Parent	T1	Cat	1 = Yes; 0 = No
**Implementation Outcomes**					
*RR* Fidelity (Primary Outcome)	Rating scale	Obs	T1-T5	Cont	Proportion
Sustainment	PRESS	Para TEAM	T4-T5	Cont	Raw score
Acceptability	AIM	Para TEAM	T1-T5	Cont	Mean score
Cost	Survey	Para TEAM	T1-T5	Cont	“Ingredients approach” to measure personnel, materials, travel
**Student Outcomes (secondary outcomes)**					
Peer Engagement	POPE	Obs	T1-T5	Cont	Proportion
Social Network Inclusion	Friendship Survey	Class	T1-T3	Cont	Ratio Score
Social Skills	Teacher Perception	Teach	T1-T3	Cont	Mean score
**Organizational of School-Level Mediators**					
Implementation Leadership	S-ILS	Para Teach TEAM	T1-T5	Cont	Mean score
Implementation Climate	S-ICS	Para Teach TEAM	T1-T5	Cont	Mean score
TEAM Processes	TPS	TEAM	T1-T5	Cont	Mean score

### Participants

We will recruit 55 elementary schools across Washington, California, and Oregon. To be eligible, schools must have at least two educators directly involved with *RR* implementation, and at least two autistic students and/or students who are isolated, rejected, or peripheral on their classroom social network.

#### Inclusion/exclusion

We will recruit *n* = 121 educators who attend recess and are school district employees, to ensure they have the capacity to participate in research activities. We also will recruit *n* = 55 general and/or special education teachers to complete study measures about students and school-level constructs and *n* = 83–138 other school personnel (e.g., administrators, teachers) to serve on the school-based teams (approximately 3–5 participants). Participants will remain in the study for 18 months unless they withdraw or change jobs. School personnel involved with *RR* coaching will receive $50 for their data completion. School personnel involved with school-based teams will receive $25 per session and $25 for their data completion. Teachers will receive $25 for their data completion and an additional $10 per student per data collection timepoint.

We will recruit 118 autistic students and allistic classmates. Autistic students will be included if they: 1) have a documented autism classification; 2) are between the ages of 5–12 and enrolled in Kindergarten through 5th grade; and 3) share a recess period with allistic peers. Allistic classmates will be included if they are: 1) isolated or peripheral on their classroom social network; and 2) require support during recess. Autistic students and their peers without an available educator supporting recess will be excluded. Participants will not be excluded given their sex, gender identity, age, or racial/ethnic background, and will not be asked to disrupt any other service utilization.

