#### Data collection

Data will be collected during the following timepoints: T1 = baseline; T2 = Exit of *RR* 1; T = 3 End of Year 1; T4 = fall, the following school year; and T5 = spring, the following school year***.*** At baseline, we will collect demographics from all participants, as well as time in inclusion from teachers and autism symptomatology from caregivers. We also will ask caregivers to rate the quality of play for their child at all timepoints (T1-T5). A masked rater will code *RR* fidelity and peer engagement at all timepoints (T1-T5) provided the student remains at the school the following year. Educators and school-based teams members will be asked to complete acceptability and a cost survey at T1-T5 and rate sustainment at T4-T5. All consented students will be administered the Friendship Survey (~ 5–10 min) at T1-T3, and teachers will be asked to complete a measure of social skills per enrolled student at T1-T3. We will continue to collect implementation outcomes the following school year. Educators, teachers, and school-based team members will be asked to rate implementation leadership and climate and team processes at T1-T5. Participants will be assigned a numerical code. De-identified data will be entered into REDCap, and all efforts will be made to prevent risks. Progress reports will be submitted as required. De-identified data will be shared with the National Database for Autism Research twice a year.

Schools will receive an initial 60–90-min didactic at the start of the school year, followed by 20–30 min of weekly coaching. *RR* experts will provide both the initial training and weekly coaching via Zoom. Research staff will receive training to reliably administer measures and achieve coaching and school-based teams fidelity.

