#### Organizational mediators

*Implementation Leadership.*Educators will complete the School Implementation Leadership Scale (S-ILS) [72], a 21-item measure that assesses seven subscales of implementation leadership: knowledgeable (understanding of *RR* and implementation issues), supportive (support for *RR* use), proactive (anticipating and addressing challenges), perseverant (consistent and responsive to challenges), communicative (shares implementation related information with staff), has a vision/mission (oriented towards using *RR*), and available in implementing *RR* [39, 75]. The S-ILS is a psychometrically validated and reliable instrument (α = 0.95–0.98). Implementation leadership is scored using aggregate individual ratings to the school level.

*Implementation Climate*. Participating educators will complete the School Implementation Climate Scale (S-ICS) [76], a 21-item measure that assesses seven subscales of implementation climate: focus, educational support, recognition, rewards, use of data, existing supports, and *RR *integration [75, 76]. The S-ICS is a psychometrically validated and reliable instrument (α = 0.81–0.91; 39, 79). Implementation climate is scored using aggregate individual ratings to the school.

*Team Processes.* TEAM members will complete the Team Processes Survey (TPS) [77] short form, a 10-item self-report of team processes (mission analysis, goal specification, strategy formulation and planning, monitoring progress toward goals, systems monitoring, team monitoring and backup, coordination, conflict management, motivation, and confidence building, and affect management). Responses are structured on a 5-point Likert-type scale from “1” = not at all to “5” = to a very great extent. The TPS has good internal consistency (α = 0.82–0.85). Table 4 outlines the complete study timeline, including data collection timepoints.

**Table 4 Tab4:** SPIRIT Flow Diagram

Activity	Study Period				
	**T1**	**T2**	**T3**	**T4**	**T5**
Enrollment					
Eligibility screen	X				
Informed consent	X				
Randomization	X				
Interventions					
Coaching	X	X			
TEAM	X	X			
Measures					
Demographics	X				
Autism classification	X				
Fidelity	X	X	X	X	X
Sustainment				X	X
Acceptability	X	X	X	X	X
Cost	X	X	X	X	X
Peer Engagement	X	X	X	X	X
Social Network Inclusion	X	X	X		
Social Skills	X	X	X		
Implementation Leadership	X	X	X	X	X
Implementation Climate	X	X	X	X	X
Team Processes	X	X	X	X	X

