Secondary Aim 2 aims to evaluate whether implementation leadership and climate mediates the effect of coaching with school-based teams (vs. coaching only) on *RR *fidelity and student outcomes. We will extend the regression models from Primary Aim 1 to evaluate the mediation effect [78]. The analysis will result in estimates of and confidence intervals for the direct effects for coaching with school-based teams (vs. coaching only) on outcomes and the indirect effects of the strategies on outcomes via implementation leadership and climate.

#### Secondary aim 3

Secondary Aim 3 aims to explore whether child characteristics collected at T1 moderate the effect of coaching with school-based teams vs. coaching on primary outcomes. GLMM will be expanded to include a third order interaction term (and all lower order interactions) of child characteristics (age, gender, autism classification) with strategy group (coaching with school-based teams vs. coaching only) with time (T1-T3) to evaluate the moderation effect.

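### Social skills mediation in Aim 2: the teacher who rates the outcome also rates the mediators, so a shared rating tendency can bias the indirect effect upward

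*Protocol article*

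**What the plan says.** Inclusion/exclusion recruits 55 "general and/or special education teachers to complete study measures about students and school-level constructs". For the outcome, Data collection states that "teachers will be asked to complete a measure of social skills per enrolled student at T1-T3", and Table 2 lists the teacher as the only source of social skills.

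For the mediators, Data collection states: "Educators, teachers, and school-based team members will be asked to rate implementation leadership and climate and team processes at T1-T5". The Table 2 rows for leadership and climate agree: "Para Teach TEAM T1-T5 Cont Mean score". The Organizational mediators section then says "Implementation leadership is scored using aggregate individual ratings to the school level" and "Implementation climate is scored using aggregate individual ratings to the school".

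Secondary Aim 2 will extend the Aim 1 models to estimate the "indirect effects of the strategies on outcomes via implementation leadership and climate". The outcomes are fidelity and the student outcomes, and social skills is one of those. The aim states its hypothesis for the end of Semester 2.

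On who rates climate, the Organizational mediators section is worded differently: "Participating educators will complete the School Implementation Climate Scale". Its leadership paragraph likewise names educators only.

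**The concern.** One person supplies the whole outcome and part of the mediator. A teacher who is generous or harsh on a given occasion moves both scores together, which creates a mediator-to-outcome association with no substantive link behind it. Nothing stated in Aim 2 separates the two sources. The trial could then report that leadership and climate explain gains in social skills when part of the link is one person's way of rating. Recruiting more schools would not cure this.

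The concern is confined to social skills. Fidelity and peer engagement are coded by a masked observer, and network inclusion comes from the classmates' Friendship Survey.

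**Working it through.** **1. Who rates what (Table 2, Data collection, Measures)**

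| Variable | Source | Teacher involved? |
|---|---|---|
| Leadership, climate | Paraeducators, teacher, team members | Yes |
| Social skills | Teacher | Yes, alone |
| Fidelity, peer engagement | Masked observer | No |
| Network inclusion | Class | No |

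**2. The teacher's share of the mediator score**

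Inputs from the article: 55 schools, 121 educators, 55 teachers, 83-138 team members and equal allocation, so about 27.5 schools per arm.

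- Team members per team: 83/27.5 = 3.0 and 138/27.5 = 5.0. This reproduces the article's own figure of about 3-5.
- Educators per school: 121/55 = 2.2. Teachers per school: 55/55 = 1.
- Share in coaching-only schools: 1/(1 + 2.2) = 31%.
- Share in team schools: 1/(1 + 2.2 + 3.02) = 16% down to 1/(1 + 2.2 + 5.02) = 12%.

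This treats team members as additional people and weights every rater equally.

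**3. Conditions for a false indirect effect**

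The indirect effect is a × b, where a is the arm effect on the mediator and b the mediator-to-outcome path. Shared tendency distorts b only. In a T1-T3 change model a stable tendency subtracts out, while an occasion-specific tendency with variance v adds 2 × share × v to the covariance of the two changes.

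A simulation with true b = 0 checked this. It used 55 schools, 3,000 replicates per setting, a change-score model and four team raters per team school. Assumed: unit variance per single rating, half of it school-level, and a teacher-tendency variance of 0.25 in total.

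| Tendency | a | Mean b | Mean a × b | Both paths significant |
|---|---|---|---|---|
| None | 0.5 | 0.00 | 0.00 | 4.8% |
| Stable only | 0 | 0.00 | 0.00 | 0.2% |
| Stable only | 0.5 | 0.00 | 0.00 | 5.0% |
| Occasion, v = 0.125 | 0 | 0.27 | 0.00 | 0.9% |
| Occasion, v = 0.25 | 0 | 0.49 | 0.00 | 2.6% |
| Occasion, v = 0.125 | 0.5 | 0.27 | 0.14 | 22% |
| Occasion, v = 0.25 | 0.5 | 0.51 | 0.25 | 52% |

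Without the teacher, the last two rows fall to 4-5%, with a × b about 0. As a hand check on the last row, in a coaching-only school b = [2 × (1/3.2) × 0.25] / [2 × 0.5/3.2] = 0.156/0.3125 = 0.50.

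This run shows which conditions matter. It does not forecast the size, because its settings are strong. With outcome noise of 0.15 per occasion, the teacher's two changes correlate 0.25/√(0.75 × 0.55) = 0.39 for v = 0.125 and 0.50/√(1.00 × 0.80) = 0.56 for v = 0.25. Apart from the arm effect, schools also have no true change of their own in the mediator.

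**4. Size under more moderate assumptions**

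Second simulation: 55 schools, two educators and one teacher rating climate, four team raters added in team schools, and two rated students per school. True b = 0, team effect on climate 0.8 school SD, and school ICC of climate ratings 0.1-0.3. The correlation r between the teacher's rating tendency and her social skills ratings, after baseline adjustment, is assumed. 3,000 replicates per setting, school-mean regressions.

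| r | Path b falsely significant | Both paths |
|---|---|---|
| 0.1 | 6-7% | 3-4% |
| 0.2 | 8-13% | 5-6% |
| 0.3 | 14-24% | 8-9% |
| 0.4 | 20-35% | 12-13% |
| Teacher left out | about 5% | 2-3% |

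If the team raters are ignored, the path figures for r = 0.2, 0.3 and 0.4 rise to 11-17%, 20-32% and 30-49%. Those overstate the problem, because the article has team members rate.

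**The case against.** **A stable rating style cancels.** The Aim 1 contrast is change from T1 to T3, and Aim 2 extends those models. This stands for a purely stable tendency when mediator and outcome both enter as change. It does not cover a tendency that varies by occasion. The article also does not say that the mediator enters as change. The Aim 2 hypothesis refers to the end of Semester 2, so a model on T3 levels is not excluded.

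**A false indirect effect needs an arm effect on the mediator.** True, and without one the joint error rate stays low. But the Theoretical framework section expects teams to act on leadership and climate, so the bias is active in the scenario the trial hopes for.

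**Other raters dilute the teacher, and the correlations are assumed.** Both points stand. The scales also rate different objects: a school's support for the intervention and a child's social behaviour. The article gives no correlation, and at 0.1 there is little to correct.

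**Perhaps teachers do not rate the mediators.** The abstract counts educators (assistants, aides) separately from teachers. If the Organizational mediators wording governs in that sense, the overlap disappears. But Inclusion/exclusion, Data collection and Table 2 all include teachers, and Table 2 also lists paraeducators, teachers and team members together under educator characteristics. The word does not settle the matter, which is a reason to reconcile the statements.

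**Which raters enter the score is analysis-plan detail.** Partly so. However, the article itself fixes the raters, the aggregation and the mediation test, and the overlap follows from those three.

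**Conclusion.** The overlap is stated in the article, and it can bias the Aim 2 indirect effect on social skills upward. Two conditions are needed together: a tendency that survives the adjustment (occasion-specific, or a model on T3 levels), and an arm effect on leadership or climate. Under assumed correlations of 0.2-0.4 with team raters included, the mediator-to-outcome path is falsely significant in about 8-35% of trials. The joint test is falsely significant in about 5-13%, against 2-3% without the teacher. These figures rest on the assumed correlations, ICC and arm effect, and on one teacher per school, inferred from 55 teachers in 55 schools.

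A reader might go further and infer that mediation will be found regardless of the truth, or at the 22-52% rates in step 3. The documents do not support that: a stable style largely cancels in change, and those rates come from strong assumed settings. Nor do they support doubt about the rest of Aim 2 or about the primary analysis, because none of those outcomes is rated by the teacher. This is a modest point about one outcome in a secondary aim, worth acting on because the correction is cheap.

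**What to change.** For the Aim 2 model with social skills as the outcome, compute school-level leadership and climate without the teacher who rates the students. At minimum, prespecify this as a sensitivity analysis. Keep the educators and the team members: they do not rate social skills, so this fault gives no reason to drop them. In team schools, using the 2.2 educators alone would discard 3-5 team raters as well as the teacher. The full rater set can stay for all other outcomes.

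Also reconcile the Organizational mediators section with Table 2 and Data collection on who completes the leadership and climate scales.

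The cost is wording only, with no new data. The mediator loses one rater per school, so it is slightly less reliable in this model, and it differs slightly from the score used for the other outcomes, which should be noted when indirect effects are compared.
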